## 5.3 Study procedures

The tests will be performed in the Martini Ziekenhuis. A family member is allowed to be present if desired. The patients will be asked to arrive in the Martini Ziekenhuis around a scheduled time of levodopa administration. In order to be able to measure during an *off* period, patients will be asked to postpone the intake of the scheduled levodopa until they become *off*. As soon as the patient starts feeling *off*, explanation of the test procedure will be started. Because becoming *off* is not one fixed point in time but will take a while, a 15 minute waiting period before start of the inhalation test will be taken. During this waiting period, the researcher will explain the test procedure. The patient will receive instructions

**Investigation of the applicability of dry powder inhalation in patients with Parkinson's disease.**

---

on how to use the test inhaler. The instructions will be given orally and partly be demonstrated by the instructor, partly be visualised by photographs and recordings of generated flow curves on a computer screen. 15 minutes after the patients started to feel *off*, a motor function examination will be performed. We prefer to start the inhalation tests when the UPDRS III motor score is at least 30 (out of 56). However, if the patient does not reach a UPDRS III motor score of 30 after a 2 hour waiting time, inhalations tests will start if the UPDRS III motor score is at least 25. In this study, three resistances will be used for the inhalation tests, (one resistance comparable with the resistance of the TwincerTM, one higher and one lower resistance). A maximum of ten flow curves will be collected (for the three resistances together). After they finish the test inhalations, the patients will take their levodopa. They will leave the hospital only when they are in an *on* period.

*Test 1: Motor function examination*

The Unified Parkinson's Disease Rating Scale (UPDRS) (see appendix 2) is a tool to assess severity of symptoms in Parkinson's disease (Pal et al, 2013). The UPDRS is the primary outcome measure in most clinical trials of Parkinson's disease therapeutics (Tavares et al, 2005). The UPDRS consists of six sections, in which all items (unless otherwise indicated) are rated from zero (normal) to four (severely affected).

The UPDRS consists of six sections, in which all items (unless otherwise indicated) are rated from zero (normal) to four (severely affected).

Since motor symptoms (rigidity, bradykinesia) are major symptoms during an *off* period, the UPDRS III motor examination section will be useful to assess the clinical state of motor function immediately before the inhalation tests will start. The UPDRS motor examination section is a 14-item rating of motor signs. It rates tremor, facial and generalized bradykinesia, and performance on several straightforward tasks (Factor et al, 2002). Each item is rated from zero (normal) to four (severely affected).

In this study, an accredited UPDRS scorer will rate the UPDRS III motor section for each patient, immediately before the inhalation tests will start. This allows the researchers to specify the motor function during inhalation. We prefer to start the inhalation tests when the UPDRS III motor score is at least 30 (severe Parkinson). However, if the patient does not reach a UPDRS III motor score of 30 after a 2 hour waiting time, inhalations tests will start if the UPDRS III motor score is at least 25.

*Test 2: Recording of the inhalation curve through the test inhaler with standard mouthpiece and (medium) air flow resistance*

The patient will be instructed to first breath out completely (turning the face away from the test inhaler) and then breath in firmly and as long as possible through the test inhaler. Additionally, the patient will be asked to hold the breath for at least 3 to 5 s (if possible). A few inhalations will be practiced before recording of the first curve (and breath hold period) during which the patient can see the flow curve of his/her performance on the computer screen. This gives the opportunity to explain and illustrate how the inhalation manoeuvre can be improved.

When the patient has finished all his/her inhalations (maximum of 10 inhalations; excluding practicing before recording will start), the test inhaler and the mouthpiece that were used will be cleaned and disinfected with ethanol and be allowed to dry prior to using them for the next patient.

#### **5.4 Withdrawal of individual subjects**

Subjects can leave the study at any time for any reason if they wish to do so, without any consequences. The investigator can decide to withdraw a subject from the study for urgent medical reasons.

#### **5.5 Replacement of individual subjects after withdrawal**

Individual subjects will be replaced after withdrawal, until a number of 15 patients are reached.

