### **4.4 Sample size calculation**

The study is an observational study designed to obtain insight into the ability of Parkinson's patients to use a dry powder inhaler during *off* periods.

We based our sample size calculation on previous studies performed in Parkinson's disease. Canning et al (1997) evaluated exercise capacity, respiratory function and gait in 16 patients with mild to moderate Parkinson's disease. Guedes et al (2012) investigated the MIP and MEP in 26 patients with Parkinson's disease during *on* and *off* periods of levodopa compared to healthy volunteers. Seccombe et al (2011) recruited 19 patients with mild-moderate Parkinson's disease without respiratory disease and assessed ventilatory control. Since we only want to obtain insight into the ability of Parkinson's patients to use a dry powder inhaler during *off* periods, 15 patients valid for evaluation is sufficient.

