## 5. METHODS

### 5.1 Study parameters

#### 5.1.1 Main study parameters

The main study parameter is to determine if a Parkinson's patient can operate a test inhaler correctly during *off* periods, by testing if they can generate a sufficiently large airflow and volume through the test inhaler *theoretically* necessary to disperse a medicinal powder and transport the aerosol into the lower airways during an *off* period.

The parameter that describes whether or not a patient is capable of using the inhaler correctly is the (duration of the) pressure drop (s)he creates over the inhaler upon inhalation. For the Twincer™ a pressure drop between 2 kPa and 4 kPa is optimal. The main study parameter therefore is the capability of patients to create a pressure drop between 2 kPa and 4 kPa by using a test inhaler with the resistance comparable with the Twincer™. At least 11 out of 15 patients should be able to create a pressure drop between 2kPa and 4 kPa, when using the resistance comparable of the Twincer™.

From the pressure drops created with the three resistances, the following parameters (which give more insight in the inhalation profile) will be calculated:

- Peak and mean inspiratory flow rate (PIFR and MIFR).
- Acceleration towards peak inspiratory flow rate (flow increase rate: FIR).
- Inhaled volume.
- Total inhalation time.

The data obtained with the test inhaler (by using the three resistances) could be used to optimise the Twincer™ DPI for Parkinson's patients. Specific characteristics of the Twincer™ could be adjusted to what Parkinson's patients can do with a DPI, in order to realise a DPI with levodopa that Parkinson's patients can operate during the *off* phase. Such characteristics are for example the resistance, the dose and the emission profile. With this new knowledge we aim to develop a DPI with levodopa for Parkinson's patients.

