#### **5.6 Premature termination of the study**

The study will be terminated prematurely if the number of withdrawals is more than 5 of the included Parkinson's patients for whatever reason. This means that when 6 Parkinson's patients are withdrawn from the study during the measurements, the study will be terminated.

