**Investigation of the applicability of dry powder inhalation in patients with Parkinson's disease.**

---

The tests will be performed with a dummy test inhaler without any drug substance or excipient. Therefore, the risks of the test procedure itself are negligible. If a patient experiences unease or discomfort at any time during the test or the exercise inhalations, the test will be stalled immediately. Adverse events are defined as any undesirable experience occurring to a subject during the study, whether or not considered related to the test procedure. All adverse events reported spontaneously by the subject or observed by the investigator or his staff will be recorded. The possibility of the occurrence of serious adverse effects caused by use of the test inhaler is excluded by the use of a dummy test inhaler without drug or excipient.

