**7. STATISTICAL ANALYSIS****7.1 Descriptive statistics**

Routine descriptive statistics of the subject characteristics (e.g. age, gender, weight, length, UPDRS III score) will be presented. The capability of the Parkinson's patients to generate a sufficiently large pressure drop will be described qualitatively.

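### Replacing every withdrawn patient, whatever the reason, can drop from the 11-of-15 criterion patients who withdraw because they cannot do the inhalation

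*Protocol*

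**What the plan says.** Five sections of the protocol bear on who makes up the 15.

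- **Replacement (5.5):** "Individual subjects will be replaced after withdrawal, until a number of 15 patients are reached". No reason for withdrawal is excepted.
- **Withdrawal (5.4):** "Subjects can leave the study at any time for any reason if they wish to do so". The investigator may also withdraw a subject, but only for urgent medical reasons.
- **Sample size (4.4):** the target is expressed in evaluable patients: "15 patients valid for evaluation is sufficient".
- **Success criterion (5.1.1):** "At least 11 out of 15 patients should be able to create a pressure drop between 2kPa and 4 kPa", at the resistance comparable to the Twincer.
- **Study stop (5.6):** "The study will be terminated prematurely if the number of withdrawals is more than 5 of the included Parkinson's patients for whatever reason". Five withdrawals are tolerated and the sixth ends the study.

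Two further passages matter for what is left open. Section 6.2 states: "If a patient experiences unease or discomfort at any time during the test or the exercise inhalations, the test will be stalled immediately". It does not say whether such a patient is then withdrawn, replaced or counted. Section 7.1 limits the analysis to description: "The capability of the Parkinson's patients to generate a sufficiently large pressure drop will be described qualitatively". Nothing there says how a patient without a usable curve enters the count.

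**The concern.** In most studies, replacing withdrawals costs little because leaving says little about the outcome. Here the outcome is whether a patient in the off phase can perform the manoeuvre. A patient who begins the practice or recorded inhalations and leaves because they cannot manage them has given an answer to the study question, and the answer is no. Under section 5.5 that patient is exchanged for another, and the criterion is read on the 15 who remain.

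The path is open in the procedures. Section 5.3 puts practice inhalations before the first recorded curve, so a patient can fail there and leave no data. Section 5.6 itself refers to withdrawals during the measurements.

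The result is meant to inform whether the Twincer needs adapting for this population (sections 1.3 and 5.2). Patients who cannot cope with the manoeuvre are the ones who would show that need. With only 15 patients, moving one or two between replaced and failed can change whether 11 is reached.

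**Working it through.** **The plan's own figure.** 11/15 = 73.3%, with an exact (Clopper-Pearson) 95% interval of 44.9% to 92.2%. The cut-off itself cannot be re-derived: the protocol gives no null rate, target rate, alpha or power, and section 4.4 bases the 15 on the sizes of earlier studies.

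**Range allowed by the protocol's own rules.** Inputs: 15 evaluable patients (4.4, 5.5), at least 11 successes (5.1.1), at most 5 withdrawals replaced (5.6). Let *w* be the number of replaced patients who withdrew because of inability. With exactly 11 successes, the rate among all who started is 11/(15 + *w*):

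| *w* | Reported | Among all who started | Exact 95% CI |
|---|---|---|---|
| 0 | 11/15 = 73.3% | 11/15 = 73.3% | 44.9 to 92.2% |
| 1 | 11/15 = 73.3% | 11/16 = 68.8% | 41.3 to 89.0% |
| 2 | 11/15 = 73.3% | 11/17 = 64.7% | 38.3 to 85.8% |
| 3 | 11/15 = 73.3% | 11/18 = 61.1% | 35.7 to 82.7% |
| 4 | 11/15 = 73.3% | 11/19 = 57.9% | 33.5 to 79.7% |
| 5 | 11/15 = 73.3% | 11/20 = 55.0% | 31.5 to 76.9% |

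The largest gap is 73.3 − 55.0 = 18.3 percentage points.

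**Chance of meeting the criterion.** This needs two assumptions that the protocol does not supply: the true ability π among all who start, and the share *f* of unable patients who withdraw without a usable curve and are replaced. All other withdrawals are taken as absent.

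- Withdrawal probability per patient: ω = (1 − π)*f*.
- Success rate among evaluable patients: q = π/(1 − ω).
- Probability that 15 evaluable patients are reached before a sixth withdrawal: C = Σ over k = 0 to 5 of (14 + k choose k) ω^k (1 − ω)^15.
- Chance of meeting the criterion: C × P(X ≥ 11), with X binomial (15, q). The product is valid because, given that a patient is evaluable, success does not depend on how many withdrew.

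For π = 55%:

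| *f* | ω | q | P(X ≥ 11 of 15) | C | Study ends early (1 − C) | Chance of meeting 11/15 |
|---|---|---|---|---|---|---|
| 0 | 0 | 55.0% | 12.0% | 100% | 0% | 12.0% |
| 25% | 11.25% | 62.0% | 26.6% | 98.1% | 1.9% | 26.1% |
| 50% | 22.5% | 71.0% | 54.9% | 71.6% | 28.4% | 39.3% |
| 75% | 33.75% | 83.0% | 90.4% | 28.4% | 71.6% | 25.7% |

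Other values of π show the same pattern. At π = 50% the chance goes from 5.9% (*f* = 0) to 15.2% (*f* = 25%) and 24.9% (*f* = 50%). At π = 60% it goes from 21.7% to 40.0% and 55.2%.

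**The case against.** The strongest reply has four parts.

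**Most failures are counted.** A reader might infer that only patients able to use the inhaler can enter the 15. The protocol does not support that. A patient who inhales and falls outside 2 to 4 kPa has a recorded curve and stays in as a failure. Up to ten curves may be recorded and no minimum is set, so a patient who tires after one or two need not be a withdrawal. This stands: the problem is confined to patients who leave without a usable curve at the Twincer-like resistance.

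**Stalling a test is not withdrawal.** A reader might join sections 6.2, 5.4 and 5.5 into a rule that anyone who stops for discomfort is withdrawn and replaced. The protocol does not say so. Section 6.2 leaves that patient's status undefined, and inability is not among the investigator's grounds in section 5.4. This stands too. It does not remove the point, because the patient may leave for any reason and section 5.5 then replaces them.

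**The sixth-withdrawal stop limits the harm.** The column P(X ≥ 11 of 15) might be read as the chance of a false success, reaching 90% at *f* = 75%. That ignores section 5.6. Under the stop, 72% of such studies end early and the chance is 26%. The cap bounds the bias, but it acts only at the sixth withdrawal and takes no account of reason.

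**The stakes are modest.** The session is short (30 minutes at most), only air is inhaled, there is no hypothesis test and the outcome is described qualitatively. Ability-related withdrawals may be few or none. This weighs on severity. It does not justify leaving the rule open, since section 5.1.1 does state a numerical criterion.

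**Conclusion.** The point holds in a limited form. Section 5.5 replaces withdrawals without regard to reason while the criterion in section 5.1.1 measures the very ability whose lack may cause withdrawal. The success rate can therefore be overstated, and the error can only run upward.

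The size is conditional. With no ability-related withdrawal there is no bias. One such withdrawal alongside 11 successes means 69% reported as 73%. The worst case under the protocol's own rules is 55% reported as 73%, and it requires all five tolerated withdrawals to be due to inability. Assuming 55% true ability and applying the stop at the sixth withdrawal, the chance of meeting 11 of 15 rises from 12% to 26%, 39% or 26% when a quarter, a half or three quarters of unable patients withdraw and are replaced; 2%, 28% and 72% of studies then end early. The 55% and those shares are assumptions.

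The point should be fixed. It is not grounds for holding up the study: the outcome is descriptive, the bias is capped, and whether it occurs at all depends on events the protocol cannot predict. A statistical analysis plan could add a sensitivity count, but who is replaced is an enrolment rule and belongs in the protocol.

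**What to change.** Amend section 5.5 along these lines:

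1. Replace only patients who leave before their first inhalation attempt, or who stop for a technical reason or a reason documented as unrelated to the manoeuvre.
2. A patient who has begun practice or recorded inhalations, and stops because they cannot perform or tolerate the manoeuvre without having produced a qualifying curve at the Twincer-like resistance, is not replaced and counts as a failure among the 15.
3. List every withdrawal and every stalled test with its reason, and also report the success rate among all who started inhaling.

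The amendment should name the role that classifies the reason, because off-phase symptoms such as pain or restlessness could be mistaken for inability. It should also say whether patients counted as failures under item 2 add to the withdrawal count in section 5.6.

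**Cost.** A few sentences in the protocol and a reason field on the case report form. The reported success rate may be lower, and someone must judge and record why a patient stopped. Only the counting changes; the patient's right to stop at any time is untouched.

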#### **5.6 Premature termination of the study**

The study will be terminated prematurely if the number of withdrawals is more than 5 of the included Parkinson's patients for whatever reason. This means that when 6 Parkinson's patients are withdrawn from the study during the measurements, the study will be terminated.

## 6. SAFETY REPORTING

### 6.1 Section 10 WMO event

In accordance to section 10, subsection 1, of the WMO, the investigator will inform the subjects and the reviewing accredited METC if anything occurs, on the basis of which it appears that the disadvantages of participation may be significantly greater than was foreseen in the research proposal. The study will be suspended pending further review by the accredited METC, except insofar as suspension would jeopardise the subjects' health. The investigator will take care that all subjects are kept informed.

### 6.2 Adverse and serious adverse events

Despite optimized treatment, many Parkinson's patients still suffer from *off* periods. In the IMPACT registry, which enrolled a large number of patients who were experiencing *off* periods, patients experienced approximately three *off* periods per day. The mean duration of these *off* periods was approximately 50 minutes (Stacy et al, 2006). Most Parkinson's patients are used to have frequent *off* periods.

In order to be able to test the ability to use a dry powder inhaler correctly during an *off* period, patients will be asked to postpone the intake of levodopa until they become *off*. Since the half life of levodopa is very short (+/- 90 min) (Nutt, 2008), we expect a patient will become *off* shortly after the planned levodopa dose. As soon as the patient starts feeling *off*, explanation of the test procedure will be started. Because becoming *off* is not one fixed point in time but will take a while, a 15 minute waiting period before start of the inhalation test will be taken. During this waiting period, the researcher will explain the test procedure. 15 minutes after the patients started to feel *off*, the motor function examination will be performed. We prefer to start the inhalation tests when the UPDRS III motor score is at least 30 (out of 56). However, if the patient does not reach a UPDRS III motor score of 30 after a 2 hour waiting time, inhalations tests will start if the UPDRS III motor score is at least 25. After they finish the test inhalations, they will take their levodopa. The total test procedure (explanation, motor function examination, inhalations) will take not more than 30 minutes. Patients will leave the hospital only when they are in an *on* period. Since all patients included are familiar with frequent *off* episodes, no new discomfort compared to other *off* episodes is expected. The timeframe between the morning levodopa dose and the postponed levodopa dose is expected to be shorter than the levodopa free period during the night. The participating patients are therefore used to a levodopa free period and the effect of a levodopa free period on their motor function.

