**Nature and extent of the burden and risks associated with participation, benefit and group relatedness:** The inhaler to be used is a specially designed dummy without drug or excipient, so the Parkinson's patient will not inhale anything but air during the test. The burden is minimal as the procedures are limited to the performance of a couple of inhalations (maximum 10). Per Parkinson's patient, the test is limited to one test moment that lasts maximally 30 minutes per test moment. This observational study has no specific benefits for the participating Parkinson's patients. Only when performed in this population, information on the inspiratory capacities of Parkinson's patients can be obtained. Since all patients included are familiar with frequent *off* episodes, no new discomfort compared to other *off* episodes is expected. The timeframe between the morning levodopa dose and the postponed levodopa dose is expected to be shorter than the levodopa free period during the night. The patients are used to a levodopa free period and the effect of this levodopa free period on their motor function.

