### 3. STUDY DESIGN

The study is a non-therapeutic observational study in which the applicability of dry powder inhalation in Parkinson's patients will be investigated. The study will be conducted with an instrumented test inhaler. The test inhaler concept is a dummy, without any drug substance or excipient. It is equipped with a pressure drop meter to record the inhalation curve of the patient. A more extensive description of the test inhaler is given in the introduction and in paragraph 5.2 *Test inhaler*.

The duration of the study is approximately 12 months (different days) and will be conducted at the Martini Ziekenhuis. Only Parkinson's patients who are under treatment by a neurologist in the Martini Ziekenhuis are able to join. For the individual patient, the test will last maximally 30 minutes (including instruction and motor function examination). The tests will be performed in the Martini Ziekenhuis.

A family member is allowed to be present during the tests. In order to be able to measure during an *off* period, patients will be asked to postpone a dose of levodopa until they become *off*. As soon as the patient starts feeling *off*, explanation of the test procedure will be started. Because becoming *off* is not one fixed point in time but will take a while, a 15 minute waiting period before start of the inhalation test will be taken. During this waiting period, the researcher will explain the test procedure. The patient will receive instructions on how to use the test inhaler. The instructions will be given orally and partly be demonstrated by the instructor, partly be visualised by photographs and recordings of generated flow curves on a computer screen. 15 minutes after the patients started to feel *off*, the motor examination will be performed. We prefer to start the inhalation tests when the UPDRS III motor score is at least 30 (out of 56). However, if the patient does not reach a UPDRS III motor score of 30 after a 2 hour waiting time, inhalations tests will start if the UPDRS III motor score is at least 25. The patient will do a couple of inhalations with three different resistances. After the patient finished the test inhalations, the patient will take his/her levodopa. The patient will leave the hospital only in an *on* period.

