**8.4 Insurance**

As explained in the prior paragraph, the study is designed in such a way that the risks of participating are negligible. Therefore, a dispensation from the statutory obligation to provide insurance is requested. This request is enclosed in the research file (G1).

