#### 10.1.2 Analysis of potential effect.

The test inhaler is a dummy, which means it contains neither drug nor excipient. Therefore, the patient will not inhale anything but air during the tests. Furthermore, the design of the test inhaler will exclude the possibility of inhalation of any inhaler part during the tests. The test inhaler is made of polypropylene, a tough and light weight material that does not wear down, to prevent the formation of small, inhalable particles (e.g. due to dropping, thumping or screwing on the resistance disk too tightly). This material is inert to ethanol. Therefore, parts of the inhaler can be cleaned and disinfected with this liquid without degradation of the material. Moreover, we have limited the study procedures to ten inhalations that will be performed in one session of maximally 30 minutes per patient, including . explanation of the tests and the motor function (UPDRS section III) test.

In order to be able to test the ability to use a dry powder inhaler correctly during an *off* period, patients will be asked to postpone the intake of levodopa until they become *off*. Since the half life of levodopa is very short (60-90 min), we expect a patient will become *off* shortly after the planned levodopa dose. We prefer to start the inhalation tests when the UPDRS III motor score is at least 30 (out of 56). However, if the patient does not reach a UPDRS III motor score of 30 after a 2 hour waiting time, inhalations tests will start if the UPDRS III motor score is at least 25. After finishing the test inhalations, which will be performed in maximally 15 minutes, the patient will take his/her levodopa. Since all patients included are familiar with frequent *off* episodes, no new discomfort compared to other *off* episodes is expected. The timeframe between the morning levodopa dose and the postponed levodopa dose is expected to be shorter than the levodopa free period during the

night. The patients are used to a levodopa free period and the effect of this levodopa free period on their motor function.

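### The stated 30-minute maximum for the test does not cover the protocol's own wait of up to 2 hours, so time off before levodopa can reach about 135 to 150 minutes plus examination time

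*Protocol*

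**What the plan says.** **The limit.** Section 6.2: "The total test procedure (explanation, motor function examination, inhalations) will take not more than 30 minutes". Section 3: "For the individual patient, the test will last maximally 30 minutes (including instruction and motor function examination". Section 10.1.2 also speaks of a single session of at most 30 minutes and includes the explanation and the motor test in it. The Summary says that "the test is limited to one test moment that lasts maximally 30 minutes per test moment", and 8.3 again gives one session of at most 30 minutes. These last two do not say what the 30 minutes contains.

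**The procedure.** Under sections 3, 5.3 and 6.2 the explanation starts when the patient first feels off and takes place within a 15-minute wait. The motor examination follows. Testing should preferably start at a UPDRS III score of 30 or more. But "if the patient does not reach a UPDRS III motor score of 30 after a 2 hour waiting time", testing may start at a score of at least 25. The same rule is in 1.6, 3, 5.3 and 10.1.2. On the last step, 10.1.2 says: "After finishing the test inhalations, which will be performed in maximally 15 minutes", the patient takes levodopa.

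**What supports the burden claim.** Section 6.2 cites a registry in which the mean length of off "periods was approximately 50 minutes". It expects no discomfort beyond that of patients' usual off episodes, and compares the levodopa-free interval with the night. Section 8.4 asks for dispensation from insurance on the ground that "the study is designed in such a way that the risks of participating are negligible", referring back to 8.3.

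**Inhalations.** The Summary, 8.3 and 10.1.2 give ten as the maximum. Section 5.3, Test 2, reads: "maximum of 10 inhalations; excluding practicing before recording will start".

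**The concern.** The inhaler is a dummy and the patient breathes only air. The main burden of taking part is therefore the postponed dose and the time spent off. The protocol puts a number on that burden, 30 minutes, and its own procedure can exceed the number several-fold.

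The two places where a reader would look for the burden, the Summary and 8.3, give the 30 minutes and say nothing of the 2-hour wait. The insurance request in 8.4 relies on 8.3. A reader of those sections alone would not learn of the longest part of the time off. The figure of ten inhalations has the same fault on a smaller scale, because practice inhalations come on top of it.

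**Working it through.** **Inputs from the protocol**

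- Stated maximum for the test: 30 min (Summary, 3, 6.2, 8.3, 10.1.2).
- First wait, with the explanation inside it: 15 min from first feeling off (3, 5.3, 6.2).
- Wait when the score is below 30: up to 120 min (1.6, 3, 5.3, 6.2, 10.1.2). The start of the count is not defined.
- Inhalations: at most 15 min (10.1.2).
- Mean off period in the cited registry: about 50 min (6.2).
- Length of one motor examination, e: not stated. I assume 0 to 15 min.

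Sections 1.6 and 5.3 place the scoring immediately before the inhalations, so a patient who waits is taken to be scored again.

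**Step 1. Can the stated 30 min be reproduced?** If the score is at least 30 at the first examination, the time is 15 + e + inhalations. The 30 min holds if e + inhalations is at most 15 min. Since 15 min is a maximum for the inhalations, this is possible. With e = 5 min, for example, 10 min remain for the inhalations. On this direct path the limit can be met.

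**Step 2. Full wait, counted from first feeling off.** Time to levodopa = 120 + e + 15 = 135 + e.

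**Step 3. Full wait, counted after the first 15 minutes and the first examination.** Time to levodopa = 15 + e + 120 + e + 15 = 150 + 2e.

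| e (min) | Direct path, inhalations at their maximum | 2 h from feeling off | 2 h after first examination |
|---|---|---|---|
| 0 | 30 | 135 | 150 |
| 5 | 35 | 140 | 160 |
| 10 | 40 | 145 | 170 |
| 15 | 45 | 150 | 180 |

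**Step 4. Ratios at e = 0.** Against the stated maximum: 135/30 = 4.5 and 150/30 = 5.0. Against the registry mean: 135/50 = 2.7 and 150/50 = 3.0.

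**Step 5. Count started earlier.** Suppose the 2 hours run from arrival or from the postponed dose, and the patient first feels off a minutes later. Then time off before levodopa is 135 − a + e, until the 15-minute wait takes over at a = 120 − 15 = 105. The overrun is smaller, but only a patient who first feels off 105 min or more after the count starts is back on the direct path. Sections 6.2, 8.3 and 10.1.2 expect patients to become off soon after the planned dose, which suggests a small a.

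**Step 6. Inhalations.** The Summary, 8.3 and 10.1.2 count ten. Section 5.3 counts ten recorded ones plus a few practice ones, with no stated number. The total is therefore more than ten and has no stated upper limit.

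**The case against.** The strongest reply is that the 30 minutes means contact time. The parenthesis in 6.2 lists explanation, examination and inhalations, and waiting is not among them. The 2-hour rule stands two sentences earlier in the same paragraph, and also in sections 1.6, 3, 5.3 and 10.1.2, so nothing is hidden from a reader of the whole protocol. This has some force: the defect is partly an undefined term. But no passage says that contact time is meant, and the single-session wording of 8.3 and 10.1.2 fits that reading poorly. Even if it is accepted, the Summary and 8.3 still omit the longest part of the time off.

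It is also fair to say that 50 minutes is a registry mean and not a maximum, and that the protocol relies as well on familiarity with off episodes and on the night as comparator. Nothing here shows that 135 to 150 minutes exceeds the overnight levodopa-free period. Those arguments stand, although the night comparison concerns the interval without levodopa and not the time a patient feels off. The full wait applies only to patients whose score stays below 30, and any subject may leave at any time (5.4).

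Four stronger readings are tempting, and the documents do not support them:

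- *The negligible-risk conclusion depends on the 30 minutes.* Section 10.2 cites familiarity with off episodes and levodopa-free periods and the absence of any inhaled substance, with no duration. Section 6.2 draws negligible risk of the test procedure from the dummy inhaler. In 8.3 the 30 minutes is one support among several.
- *The direct path already breaks the limit because 15 + 15 leaves no time for the examination.* This treats a maximum for the inhalations as their actual length (step 1).
- *Another 30 to 60 minutes should be added for levodopa to act.* Section 1.1 gives that range for dispersible levodopa, and the protocol does not say which formulation patients take after the test.
- *Long waits will cause withdrawals and select who is tested.* This is conceivable, but the protocol gives no figure from which to judge it.

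**Conclusion.** The concern holds as a wrong figure for patient burden. The 30-minute maximum can be met by a patient who scores at least 30 at the first examination. It cannot hold as elapsed time for a patient who needs the full 2-hour wait counted from feeling off or later. For that patient, time off before levodopa is about 135 to 150 minutes plus examination time, or 4.5 to 5 times the stated figure. It is also longer than the roughly 50-minute mean off period that section 6.2 cites.

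The size rests on two things that the text leaves open: when the 2-hour count starts and how long the examination takes. An earlier start of the count would reduce the overrun but would rarely remove it. Examinations of up to 15 minutes, an assumed upper value, would raise the total to 150 to 180 minutes.

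The practice inhalations left out of the ten are a lesser inconsistency. The point should be fixed, but it touches no endpoint, no analysis and not the 11-of-15 criterion.

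**What to change.** Reconcile the passages:

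- Define whether the 30 minutes is contact time or elapsed time.
- Define when the 2-hour count starts.
- State the resulting maximum time off before levodopa in the Summary and in sections 3, 6.2, 8.3 and 10.1.2. The reference from 8.4 to 8.3 then picks it up.
- State in the same places that practice inhalations come in addition to the ten.
- Qualify the statement that no discomfort beyond usual off episodes is expected, so that it is consistent with that maximum and with the 50 minutes cited in 6.2.

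Which waiting rule should apply is for the clinical team, and no view on it is taken here. The cost is amendment text and a less favourable stated burden. No procedure is added.
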